**Data management and access**

All data management will be undertaken by the team at Homerton University Hospital. Standard operating procedures will be in place for the collection and handling of data received at the Unit. All study data will be entered into a secure, electronic trial database with restricted access. Data collected on the data collection forms and entered onto the electronic database will only identify the participants by a unique trial number.

Data will be processed on a workstation by authorised staff. The workstations access the network via a secure login and password (password changed regularly). No data will be stored on individual workstations. The Chief Investigator will ensure that this information is kept confidential. All documents will be stored securely and kept in strict confidence in compliance with the Data Protection Act (2018) for sites in the UK.

**Ethics**

The CI will ensure that this study is conducted in full conformity with the current revision of the Declaration of Helsinki (last amended October 2013) on research involving human subjects.

The CI will ensure that the trial is conducted in accordance with all applicable regulatory requirements including but not limited to the Research Governance Framework and the MRC GRP guidelines which are based on ICH Guidelines for GCP, Trust and Research Office policies and procedures and any subsequent amendments.

This trial will only start after approval from a REC, MHRA and confirmation from local R&D department has been obtained. If there is any further safety information which may result in significant changes in the risk/benefit analysis, the Protocol, PIS and ICF will be amended accordingly and submitted to REC for revision and approval.

**Data Handling and Record Keeping**

Confidentiality:

The Investigator has a responsibility to ensure that patient anonymity is protected and maintained. They must also ensure that their identities are protected from any unauthorised parties. Information with regards to study patients from UK sites will be kept confidential and managed in accordance with the Data Protection Act, NHS Caldecott Guardian, principles, The Research Governance Framework for Health and Social Care, and Research Ethics Committee Approval.

Case Report Forms:

For all participants clinical data are routinely recorded in the fertility medical notes or fertility electronic database by clinical staff. Data required for the trial will be recorded on the eCRF from these primary sources. Trained and delegated members of the trial team, as documented on the trial delegation log, will be responsible for the completion of the eCRFs. At randomisation eCRFs will be pseudonymised using a participant code. The code will be generated by the randomisation system and recorded on the Randomisation Form.

Record Retention and Archiving:

During the course of the trial, all records remain the responsibility of the Chief Investigator and must be kept in secure conditions. When the trial is complete, it is a requirement of the Research Governance Framework and Trust Policy that the records are kept for a further 20 years.

**Safety Reporting:**

Adverse events

An AE is any untoward medical occurrence in a trial participant, including occurrences which are not necessarily caused by or related to the trial intervention. An AE can therefore be any unfavourable and unintended sign (including an abnormal laboratory finding), symptom or disease temporarily associated with trial activities.

Due to the high incidence of adverse events routinely expected in this patient population and the low risk of the intervention, only those adverse events identified as serious will be recorded for the trial.

There are no expected adverse events for this intervention.

Serious Adverse events

A serious adverse event (SAE) is defined as an untoward occurrence that: (a) results in death; (b) is life-threatening; (c) requires hospitalisation or prolongation of existing hospitalisation; (d) results in persistent or significant disability or incapacity; (e) consists of a congenital anomaly or birth defect; or (f) is otherwise considered medically significant by the investigator.

The following events are foreseeable in pregnant women undergoing IVF/ICSI and hence will not require reporting as SAEs.

Events relating to the participant:

1. Ovarian hyperstimulation syndrome

2. Pelvic infection/pelvic inflammatory disease

3. Failure of frozen embryos to survive thawing

4. Multiple pregnancy

5. Miscarriage

6. Ectopic pregnancy

7. Hypertensive disorders of pregnancy

8. Gestational diabetes

9. Antepartum haemorrhage

10. Postpartum haemorrhage

Events relating to the baby:

1. Low/very low birth weight

2. Small/large for gestational age

3. Preterm/very preterm delivery

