| Methodology | Single centre, parallel arm randomised controlled trial. Following informed consent, participants will be randomised to 3 cycles of treatment or no treatment. Primary outcome is live birth rate.  Each month participants will be asked to record the first day of their menstrual period. On the relevant cycle day according to the test instructions they will start doing daily LH monitoring using a quantified validated test (same brand) until a positive result is seen. 24hrs later they will start 400mg bd progesterone (Cyclogest) pessaries (vaginal or rectal) and continue these for 14 days. After 7 days they will attend for a serum progesterone level blood test. They will then check a urine pregnancy test (validated, same brand) on the 14^th^ day after starting cyclogest (15^th^ day after LH surge). They will discontinue the progesterone if hcg is negative and those who are pregnant will continue progesterone for 38 days. 2 weeks later they will be offered an early pregnancy ultrasound.  We will gain consent to check NHS records to record live births 42 weeks after the positive pregnancy test. We will ask patients to contact us if they have a miscarriage or late pregnancy loss but will not contact them to chase for information as this does not directly impact on our measurable outcomes (clinical pregnancy rates and live birth rates). |
| Research Sites | Homerton University Hospital |
| Objectives/Aims | To assess whether luteal support with progesterone pessaries affects the likelihood of clinical pregnancy and/or live birth in natural cycles for couples with unexplained infertility |
| Number of participants/patients | 200 in total – 100 in the test group and 100 in the control group |
| Main Inclusion Criteria | Female:   - bilateral patent tubes within last 12 months (HSG/HyCoSy/Laparoscopy) - Ovulation as defined by regular cycles or ultrasound appearance of either a corpus luteum or dominant follicle or midluteal progesterone over 30nmol/ml - Regular intercourse and failure to conceive for at least 12 months   Male:   - Semen analysis with: - >15 mil/ml concentration - Motility over 40% - Progressive motility over 32% - ≥ 4% normal forms - No erectile dysfunction or other problem preventing penetrative intercourse |

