**Methodology:**

Study design:

This study is a prospective, pragmatic, two-armed, randomised controlled trial. The hypothesised benefit of the luteal phase progesterone support is to enhance endometrial receptivity and improve conception rates measured as clinical pregnancies and eventually live births.

The study does not aim to validate different formulations of progesterone or different dosing regimens. The design of the trial supports the use of progesterone as it is licensed to be used in ART cycles, at a dose of 400mg twice per day either vaginal or rectal application.

This trial will recruit eligible participants meeting the criteria for a diagnosis of unexplained infertility. All new patients seen in the fertility units will be screened for eligibility and if eligible, will be invited to participate. Following informed consent from both partners, participants will be randomised in a 1:1 ratio to either the treatment or control groups. Women will remain in the trial for three menstrual cycles and will be followed up to the end of the third cycle. If pregnant, the outcome of the pregnancy will be recorded at 6-7 weeks of pregnancy when a scan will be performed to determine clinical pregnancy and subsequently by following up live births within 6 weeks postpartum.

Study Population:

The trial will recruit and randomise 200 participants.

Study setting:

Single centre trial at the Homerton Hospital NHS trust Fertility Unit

Inclusion Criteria:

Female:

- Bilateral patent tubes within last 12 months (HSG/HyCoSy/Laparoscopy)
- Ovulation as defined by regular cycles or ultrasound appearance of either a corpus luteum or dominant follicle or midluteal progesterone over 30nmol/ml
- Regular intercourse and failure to conceive for at least 12 months

Male:

- Semen analysis with:
- >15 mil/ml concentration
- Motility over 40%
- Progressive motility over 32%
- ≥ 4% normal forms
- No erectile dysfunction or other problem preventing penetrative intercourse

Exclusion criteria:

- Age ≥42 (as likely component in infertility),
- Unilateral tubal patency
- BMI ≥30
- Abnormal uterine cavity as seen on 3D ultrasound

Primary outcome:

Live birth rates

Secondary Outcome:

Biochemical pregnancy rates (positive urine HCG test at least 14 days after starting progesterone)

Clinical pregnancy (intrauterine gestational sac confirmed on ultrasound at 6-8 weeks gestation)

Mid-luteal serum progesterone levels

Clinical efficacy outcomes/clinical safety outcomes:

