The qualified person taking consent must explain to the potential participants that they are free to refuse any involvement within the study or alternatively withdraw their consent at any point during the study and for any reason. If there is any further safety information that may result in significant changes in the risk/benefit analysis, the patient information sheet (PIS) and Informed Consent Form (ICF) will be reviewed and updated accordingly. All participants that are actively enrolled in the study will be informed of the updated information and given a revised copy of the PIS and ICF in order to confirm their wish to continue in the study (if feasible), if it may change their willingness to participate. Participants who speak limited English can only be consented and included in the trial if translation has been provided by an independent translator (i.e. not a family member) or through the Language Line translation service for UK sites. International sites have the option to translate patient-facing documentation into the required language.

Care Pathway:

Couples with unexplained infertility seen at our unit will be offered the option of self-funded IUI treatment or IVF treatment (NHS or self-funded depending on meeting eligibility criteria). Involvement in this trial will be offered to them as an option prior to self-funded treatment or whilst awaiting NHS-funded IVF treatment for which the waiting time is longer than 3 months.

Randomisation:

A computer programme will be used to randomly allocate each trial ID number to a group and patients will be randomly allocated a trial ID number using choice of a paper ticket.

Blinding: It will not be possible to blind the doctors to whether the patients have received treatment or not. The chief investigator will be responsible for organising prescriptions and given the lack of placebo, will know whether the patient has been allocated to the treatment or control group.

Trial Intervention/allocation:

Participants in the treatment arm will receive 400mg Cyclogest pessaries and will be asked to take these twice a day from 24hrs after their LH surge is detected with ovulation kits. 14 days after starting the Cyclogest they will perform a home pregnancy test and inform us of the results. If they are pregnant they will continue Cyclogest for a further 38 days as pregnancy support.

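### Congenital anomaly and death are SAE criteria, but no follow-up step after the early scan actively seeks an anomaly or a death in a liveborn baby

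*Protocol*

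**What the plan says.** **SAE scope (Protocol, Safety Reporting).** The definition opens with "A serious adverse event (SAE) is defined as an untoward occurrence that: (a) results in death" and includes the criterion "e) consists of a congenital anomaly or birth defect". The general definition of an adverse event is narrower in its subject: "An AE is any untoward medical occurrence in a trial participant". Non-serious events are not collected, since "only those adverse events identified as serious will be recorded for the trial". Three kinds of baby event are exempt from SAE reporting: low birth weight, abnormal size for gestational age, and "Preterm/very preterm delivery". Anomaly and death of the baby are not among them.

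**Follow-up after the early scan.** The synopsis (Methodology row) says: "We will gain consent to check NHS records to record live births 42 weeks after the positive pregnancy test". It also asks women to make contact about a miscarriage or late loss, and adds that the team will not pursue this information. The Study design section has the outcome recorded at the scan and "subsequently by following up live births within 6 weeks postpartum".

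**Listed outcomes.** Miscarriage, ectopic pregnancy and stillbirth are named as efficacy or safety outcomes. Anomaly and neonatal death are not.

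**Exposure (Trial Intervention/allocation).** "If they are pregnant they will continue Cyclogest for a further 38 days as pregnancy support". The synopsis gives 38 days without the word further.

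**The concern.** The protocol defines certain events as SAEs and then sets out follow-up that does not ask about them. A baby born alive with a serious anomaly, or who dies in the first days of life, is correctly counted as a live birth for the primary outcome. No planned step would bring the anomaly or the death to the trial's attention as an SAE.

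At stake is what the safety report means. Only serious events are recorded, so the SAE list is almost the whole of the safety data beyond the listed pregnancy losses. If nobody looks for these events, a blank entry cannot be told apart from a true zero, and the DMC has nothing to weigh. The trial is open-label with an untreated control, so spontaneous reporting may also differ between the arms.

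**Working it through.** **1. Events set against the steps that would find them.**

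| Event | SAE status in Safety Reporting | Step that would find it |
|---|---|---|
| Miscarriage | Exempt | Listed outcome; self-report, not chased |
| Ectopic pregnancy | Exempt | Listed outcome |
| Stillbirth | Not on the exempt list | Listed outcome; self-report of late loss, not chased |
| Congenital anomaly, liveborn | Criterion (e), not exempt | None stated |
| Neonatal death | Criterion (a) if the baby is covered, not exempt | None stated |

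The last two rows are the gap. The protocol does not say outright that the SAE definition covers the baby. Two features imply it: birth defect is a criterion, and a separate list exempts particular baby events, which would be unnecessary if baby events were out of scope.

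**2. Exposure.** Assume a 28-day cycle with the LH surge on gestational day 13.
- Start, 24 hours after the surge: 13 + 1 = day 14 (2w0d).
- Pregnancy test: 14 + 14 = day 28 (4w0d).
- End of treatment on the Trial Intervention/allocation wording: 28 + 38 = day 66 (9w3d). A surge on day 12 or 14 gives 9w2d or 9w4d.
- End if the synopsis means 38 days in total from the start: 14 + 38 = day 52 (7w3d), range 7w2d to 7w4d.

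Both readings place exposure in the first trimester, so the point does not depend on which was intended.

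**3. Timing of the record check.** 42 weeks after the test is 28 + 42 × 7 = 28 + 294 = day 322 (46w0d). Relative to the due date: 322 − 280 = 42 days. This agrees with the six weeks in the Study design section and in the End of Study Definition. For a birth at or near term, the first 28 days of life have passed by then, as has the time when an anomaly evident at birth would be noted.

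**4. Expected numbers.** The inputs are the live birth rates in the Sample size section, 7% and 24%. The plan's own figure from these rates reproduces. With pooled variance, two-sided α 0.05 and 80% power:

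n = [1.960 × √(2 × 0.155 × 0.845) + 0.842 × √(0.07 × 0.93 + 0.24 × 0.76)]² / 0.17² ≈ 70 per group.

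That figure is not in dispute.
- Live births with full follow-up of 100 per arm: 100 × 0.24 = 24 treated and 100 × 0.07 = 7 control, total 31.
- The anomaly rate is not in the documents. Assume 2–4%.
- Treated: 24 × 0.02 = 0.48 to 24 × 0.04 = 0.96 cases.
- Control: 7 × 0.02 = 0.14 to 7 × 0.04 = 0.28 cases.
- Chance of at least one case in 31 births, treated as independent: 1 − 0.98³¹ = 0.47 to 1 − 0.96³¹ = 0.72.
- With only 70 per arm followed: 70 × 0.24 = 16.8 treated births, so 0.34 to 0.67 cases.

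**The case against.** The strongest reply is that nothing stops these events being reported. Safety Reporting says serious events will be recorded. Data Collection lists clinical outcomes in general terms. The Data Monitoring Committee section lets anyone associated with the trial write in about possible harm. Staff who open the record to confirm a live birth may well see an anomaly there. All of this stands. A reader might infer that an anomaly could not be reported or would never reach the DMC, and the documents do not support that. They support the narrower statement that no step actively seeks it.

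Other stronger readings also fail:
- **Follow-up looks for live births and nothing else.** Losses are asked for and are listed outcomes, although they are not chased.
- **Counting such a baby as a live birth is wrong.** It is the declared endpoint.
- **Gestational age at delivery is a missing SAE item.** Preterm delivery is expressly exempt, so its absence contradicts nothing.
- **Unsought harm falls mainly in the treated arm.** The 24 to 7 split assumes the hypothesised benefit. With no effect, births would divide about equally.
- **The trial could compare anomaly rates.** With about one expected case or fewer per arm, it could not.

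Two limits remain. The eCRF, consent form, operating procedures and trust monitoring plan are not shown and may go further than the protocol. The protocol also does not say which NHS records are opened or whether they include the baby's. The Case Report Forms section names only fertility notes and the fertility database as sources.

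**Conclusion.** The point holds as a gap in ascertainment. Congenital anomaly is an SAE by the protocol's own definition, and so is death of the baby if, as the exempt list implies, the definition extends to the baby. The stated follow-up asks about neither. Followed as written, the plan would under-ascertain its own SAEs, and a report of none would be uninformative.

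In absolute terms the size is small: about 0.5–1.0 expected anomalies in the treated arm and 0.1–0.3 in the control arm. This rests on the planned live birth rates, full follow-up of 100 per arm, and an assumed 2–4% anomaly rate. The reason to act is that individual SAEs should be found, not that the arms could be compared. The change is cheap and should be made. It is not a matter for the SAP, because an analysis plan cannot supply data that were never collected.

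Separately, the synopsis and Trial Intervention/allocation wordings of the 38 days must be reconciled. The point above does not turn on the outcome.

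**What to change.** 1. **Synopsis (Methodology row) and Study design:** state that the record check already planned for 42 weeks after the positive test also abstracts, in both arms, congenital anomaly and neonatal death up to the check date.
2. **Safety Reporting:** state that the SAE definition covers the baby as well as the participant. Process anomalies and neonatal deaths as SAEs and report them by arm to the DMC.
3. **Consent and record access:** confirm that both extend to newborn outcomes, including the baby's record if that is where the information lies. Widen the wording if they do not.
4. **38 days:** reconcile the synopsis with Trial Intervention/allocation.

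The cost is a few data fields and a slightly longer abstraction for roughly 31 births. No extra participant visit is needed. If access to the baby's record is not already in place, obtaining it is a further cost that the protocol does not allow one to estimate.

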**Trial Committees**

Trial Management

This trial will be sponsored by the Research and Innovation Department at Homerton University Hospital. The trial will be coordinated and managed on a day-to-day basis by the Trial Management Group (TMG) comprising ofDr [name] and [name].. TheData monitoring committee (DMC) and Trial Steering Committee (TSC) will provide strategic direction. Appointment of the trial steering committee and data monitoring committee will remain the responsibility of the TMG.

Trial Management Group (TMG)

The Trial Management Group (TMG) will comprise the chief investigator and co-investigator. The TMG will be based at Homerton and will have overall responsibility for the conduct of the trial and will report to the TSC.

Summary Monitoring Plan

The study site will perform trial self-monitoring according to the agreed trust monitoring plan and self-monitoring template. The frequency and intensity will be determined by the Homerton monitoring plan and risk assessment. Trial monitoring will include source data verification checks on informed consent forms and eligibility for randomisation and a sample set of CRFs.

Audit and Inspection

A random sample of cases will be monitored. The documents to be verified will be randomly selected. Any major discrepancies found would trigger a more extensive audit of trial data. In addition, the sponsor may also carry out an internal audit throughout the duration of the trial.

Data Monitoring Committee

A single independent Data Monitoring Committee (DMC) will be established for the trial. It will comprise of an independent chair and at least two further independent members who are experts in the field, such as a clinician, trial methodologist and statistician. The DMC will meet bi-annually. Collaborators and all others associated with the trial may write through the trial office to the DMC, to draw attention to any concern they may have about the possibility of harm arising from the treatment under study, or about any other matters that may be relevant. The DMC will also monitor the progress of the trial and will report to the TSC.

Trial Steering Committee

The trial will be supervised by a single international independent Trial Steering Committee (TSC). The Trial Steering Committee (TSC) will have an independent chair and at least two further independent members. The TSC will meet biannually. The CI, co-applicants, trials coordinator and senior trials manager will be invited to attend the TSC meetings. The specific tasks of the TSC will be:

 To recommend and approve major amendments to the protocol arising during the trial.

 To receive the reports from the TMG and DMC.

 To approve the Statistical Analysis Plan and any changes thereto.

 To resolve problems brought to it by the trial collaborators.

 To approve trial reports and the main paper for publication.

**Finance and Funding:**

Cyclogest is being provided by LD Collins Ltd, the manufacturer of the product. The products will be serialised as per the Falsified Medicines Directive and will then be decommissioned by the Hospital Pharmacy before distribution to patients.

Pregnancy Tests and Ovulation kits are being provided by SPD Development Company Ltd who manufacture these.

**Indemnity:** The Homerton Hospital NHS trust will cover the indemnity for this trial.

